### Data analysis

The frequency of CD8+ T cells (cells/mm^2^) in patients receiving 2 Gy preoperative radiotherapy versus no preoperative radiotherapy will be compared using the Wilcoxon rank sum test at a one-sided significant level alpha = 0.05.

Descriptive statistics will be used to summarize the distribution of CD8+ T cell counts by treatment arm (mean, median, range, inter-quartile-range, and standard deviation).

Descriptive statistics will be used to summarize the correlation of the two the methods (IHC and flow cytometry) of quantification of T cells. IHC will be used for primary analysis for which sample size estimation was performed. Distribution of T cell subsets (CD3+, CD4+, CD45RO+, Foxp3+) and other secondary endpoints of immune response (frequencies of tumour reactive T cells and protein levels) will be evaluated with same analysis plan. Correlation in quantitative measures of immune response will be evaluated using Spearman rank correlation.

Distribution of progression free survival (PFS) and overall survival (OS) will be estimated by the Kaplan-Meier method. The treatment groups will be compared with a stratified log rank test. The effect of frequencies of tumour infiltrating CD8+ T cells on PFS and OS will be analysed using Cox proportional hazards regression. The relationship between measures of immune response and PFS and OS will be explored in multivariable Cox proportional hazard models including treatment arm as covariate.

All secondary analyses will be exploratory using two-sided significance levels alpha = 0.05.

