### Other secondary endpoints

Other secondary endpoints are digitally versus manually determined CD8+ T cell frequencies in resected NSCLC tumours, frequencies of tumour reactive T cells in blood and bone marrow before radiotherapy and after surgery, changes in the level of proteins involved in immune response in blood determined by ELISA and frequencies of CD3+, CD4+, CD8+, CD45RO and Foxp3+ T cells in resected NSCLC tumours determined by flow cytometry. Depending on the availability of pre-enrolment harvested tumour tissue, the immune contexture of these tumour biopsies will be compared to the post-radiation samples obtained from surgery. Secondary analysis will be conducted for progression free survival and overall survival as secondary endpoints, which require long-term follow-up of 6 years and will be performed and reported subsequent to the primary analysis, as well as other laboratory data derived from proteomic or transcriptomic analyses. Whole blood transcriptomics will be performed as described earlier [46]. Peripheral blood samples will be obtained before radiation, at the time of surgery, and the first visit of the patient at the radiation oncology department, the total RNA will be extracted from whole blood and the resulting expression profiles will be correlated with the immune response and clinical status of the patients. As for the proteome an array of 20 cytokines with known roles in immune response will be measured using a commercial protein array at the same three time points. Tumour reactive T cells will be determined in bone marrow aspirates by ELIPOT analysis. Bone marrow aspirates will be taken one to three days before radiation and under anaesthesia before skin incision.

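### Immune endpoints sampled before and after treatment are given the single-time rank-sum plan, with no time point or use of baseline defined

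*Protocol article*

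**What the plan says.** For the primary endpoint, the Data analysis section of the protocol article says that CD8+ density in the two arms "will be compared using the Wilcoxon rank sum test at a one-sided significant level alpha = 0.05", with descriptive statistics by arm. It extends this to the T cell subsets and adds that "other secondary endpoints of immune response (frequencies of tumour reactive T cells and protein levels) will be evaluated with same analysis plan". The section closes with "All secondary analyses will be exploratory using two-sided significance levels alpha = 0.05", so the one-sided level does not carry over to these endpoints.

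The Other secondary endpoints section describes what is measured:

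- Tumour-reactive T cells: "frequencies of tumour reactive T cells in blood and bone marrow before radiotherapy and after surgery".
- Bone marrow: "Bone marrow aspirates will be taken one to three days before radiation and under anaesthesia before skin incision".
- Blood proteins: "changes in the level of proteins involved in immune response in blood determined by ELISA".
- An array of 20 cytokines, which "will be measured using a commercial protein array at the same three time points".

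The tumour T cell subsets (CD3+, CD4+, CD45RO+, Foxp3+) come from the resected specimen, as CD8+ does. A comparison with earlier biopsies is planned only where such tissue exists.

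**The concern.** A two-sample rank-sum test takes one number per patient. For CD8+ density and the other subsets in the resected tumour there is only one number, so the plan fits. For tumour-reactive T cells and blood proteins there are two or three, and the article does not say which value or contrast enters the test. It could be the follow-up level, the change from baseline, or a baseline-adjusted value. The sections also differ on the protein endpoint: one defines a change, the other analyses a level. These are different analyses with different precision.

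Two things are at stake. The first is precision: in a trial of 15 to 18 patients per arm, stable differences between patients in blood and marrow measures stay in the error term unless the baseline is used. The second is freedom of choice: with 20 cytokines and three sampling times, an open contrast leaves room to choose after the data are seen.

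**Working it through.** **The plan's own figure.** Inputs from Sample size determination: difference 50 cells/mm², SD 50, one-sided alpha 0.05, power 80%, loss 15%.

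- Normal approximation: n per arm = 2 × (1.645 + 0.842)² × (50/50)² = 12.37.
- Allowing for the rank-sum test by its lower-bound relative efficiency: 12.37 / 0.864 = 14.3, so 15 per arm.
- Allowing for loss: 15 / 0.85 = 17.6, so 18 per arm and 36 in total.

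The stated 15 per arm and 36 in total are reproduced. They concern the primary endpoint only; the article gives no power figure for the repeated immune endpoints.

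**Inputs for the repeated endpoints.** Two-sided alpha 0.05 is from Data analysis. The 15 per arm is from Sample size determination. Two inputs are assumptions: an effect of 1 SD of the follow-up value (the ratio 50/50 used for CD8+, borrowed for illustration) and the pre/post correlation rho, for which the documents give nothing. The calculations use normal data.

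**Variance relative to the follow-up value alone.**

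| rho | ANCOVA, 1 − rho² | Change score, 2(1 − rho) |
|---|---|---|
| 0.3 | 0.91 | 1.4 |
| 0.5 | 0.75 | 1.0 |
| 0.7 | 0.51 | 0.6 |

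A plain change score helps only when rho exceeds 0.5, and below that it does harm.

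**Power.** For ANCOVA the noncentrality is √(15/2) / √(1 − rho²), with 30 − 3 = 27 degrees of freedom. This is 2.87, 3.16 and 3.83 at rho 0.3, 0.5 and 0.7. The rank-based figures are simulated and accurate to about one percentage point.

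| Analysis, 15 per arm, two-sided 0.05 | rho 0.3 | rho 0.5 | rho 0.7 |
|---|---|---|---|
| Rank sum, follow-up only | 72% | 72% | 72% |
| Rank sum, change score | 57% | 71% | 90% |
| Rank ANCOVA | 74% | 82% | 93% |
| ANCOVA | 79% | 86% | 96% |

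Simulating ANCOVA directly gives 78%, 85% and 95%, in agreement with the formula.

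Part of the gain from rank sum to ANCOVA comes from using a parametric test on normal data: a two-sided t test on follow-up alone already has 75%. The like-for-like gain from adding the baseline is therefore 72% to 74%, 82% and 93% on ranks, or 75% to 79%, 86% and 96% on the measured scale. At 18 per arm, rank sum on follow-up alone has about 80%.

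**The case against.** The strongest reply is that the article fixes no wrong method. A rank-sum test can be run on changes as well as on levels, and the choice of contrast for exploratory biomarkers is often left to an analysis plan, which is not shown here. The protein endpoint is defined as a change, so a test of it would use the baseline. With 1:1 randomisation, a rank-sum test on follow-up values is valid, and a rank-based test is a sensible choice for skewed assay data in a small trial. The effect size and the correlation behind the power figures are not from the documents.

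Most of this stands, and it rules out three stronger readings. A reader might infer that the plan ignores the baseline values, but the text does not say so, and the definition of the protein endpoint points the other way. A reader might infer a between-arm test at baseline, but none is stated. A reader might infer that chance baseline imbalance biases the result, but it is part of the sampling variability that the test already allows for.

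The appeal to an unseen analysis plan does not dispose of the point. The article assigns these endpoints a plan built for a single measurement, and its two sections disagree on whether the protein endpoint is a level or a change.

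**Conclusion.** The point holds as a minor one. The article carries a single-time, two-arm plan over to endpoints measured before and after treatment, names no time point or baseline term for them, and describes the protein endpoint in two ways that do not match. If follow-up values alone are tested, the result is valid but less precise than it could be. For a 1 SD effect at 15 per arm, the power given up is about 2 to 21 percentage points against rank ANCOVA and about 7 to 24 against ANCOVA, over rho 0.3 to 0.7. These sizes rest on the assumed effect, the assumed correlations and normal data. With a low correlation the gain is small.

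The endpoints are exploratory and two-sided. The primary CD8+ comparison, its one-sided test and the sample size are unaffected.

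**What to change.** For each immune endpoint with a pre-treatment value, name the post-treatment time point and compare the arms there by ANCOVA on log values, or by rank ANCOVA, with the patient's own baseline as covariate, two-sided 0.05 and exploratory. Use the same description of the protein endpoint in Other secondary endpoints and in Data analysis. Keep the rank-sum test for the T cell subsets measured once in the resected tumour.

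No patients or assays are added where the baseline samples are already planned. The cost is a little more analysis work and a modelling assumption: a linear relation to baseline on the log or rank scale.

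There is one condition. The adjustment works only where control patients have a matching baseline sample, and Other secondary endpoints times that sample relative to radiation, which controls do not receive. The same section places the later T cell measurement after surgery but the second marrow aspirate before skin incision, while Preoperative assessment describes marrow sampling at admission the day before surgery. These statements must be reconciled before the analysis is fixed.

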### Data management and quality assurance

The Department of Thoracic Surgery at Thoraxklinik and the Molecular and Radiation Oncology Department of the German Cancer Research Center and University Hospital Heidelberg coordinate this trial. Data regarding T cell detection in blood and bone marrow of all patients will be entered in a password-protected database at the Department of Thoracic Surgery at Thoraxklinik and at the German Cancer Research Center. The clinical and laboratory data of all included patients will be centrally collected in a password-protected database located at the Department of Thoracic Surgery at Thoraxklinik.

## Discussion

Non-small cell lung cancer (NSCLC) has still a poor prognosis. Even in patients with radically operated stage I NSCLC the 5-year recurrence-free rate only is about 75 % [8]. The development of additional treatments represents an unmet medical need for patients with completely resected NSCLC. Preclinical cellular immunotherapeutic approaches demonstrated the ability to reject solid tumours by tumour specific T lymphocytes [15, 48], the effectiveness of these approaches, however, could not be translated into clinical trials so far. Insufficient migration and activation of tumour infiltrating lymphocytes are considered the main reasons for inadequate host anti-tumour immune response. Lung cancer is supposed to exhibit a particular immunosuppressive microenvironment. Low dose ionizing radiation stimulates a localized pro-inflammatory milieu thereby modulating the tumour microenvironment. The results of this trial could demonstrate a beneficial immune related effect and suggest low dose radiation to be a complementary neoadjuvant component of immunotherapy prior to surgery in operable NSCLC with only mild side effects in future. However this needs to be investigated in larger trials. The goal of this randomized trial is to assess if combining preoperative low dose radiation and surgical removal of early stage non-small cell lung cancer will improve host anti-tumour immune response. If successful, a combination of immune modulatory treatments, such as ionizing radiation and checkpoint inhibition may help to reverse the process of immunosuppression in NSCLC and could therefore be an integral treatment strategy in NSCLC.
